#### Step 2: randomizing clients who consent

Upon a client’s signed release of information and consent forms, they are eligible for randomization. Logic within the CRCT system randomizes the participants to one of two groups with 0.5 probability: the treatment group or the control group. Due to the limited fields in CRCT available at intake, we did not conduct stratified randomization. Each group then proceeds to their respective intervention.

#### Step 3: treatment group participants receive the intervention

#### Step 4: both treatment and control group participants complete the life-course history survey

We invite participants in both groups, using a standard script, to complete our life-course history survey measuring demographics, polysubstance use, mental health, and several other topics discussed in greater detail later.

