### Aims and objectives

We focus on the causal impact of an intervention: an offer of hands-on-help with using an ODR tool to resolve legal issues. Our primary aim is focused on the most proximate effect of the intervention: the client’s compliance with goals he or she has set for their own treatment and recovery. We will also explore whether the impact (or lack of detectable impact) on recovery outcomes is accompanied by impacts on more distal outcomes in clients’ ability to secure stable housing, employment, and family reunification.

More specifically, the project intends to answer the following questions:

**Primary question**: does offering clients access to and hands-on-guidance with ODR to resolve legal issues increase the client’s likelihood of completing treatment?**Secondary questions**: our ability to investigate these questions depends on data linkages that are still in process. If we are successful obtaining administrative data, we intend to investigate the impact of offers and receipt of hands-on help on the following outcomes, at years one and two following the intervention:
Utilization of healthcare/SUD services.Employment.Housing.Family reunification.Mortality.
**Heterogeneous effects**: focusing on the primary question, do we see heterogeneous effects across the following subgroups of clients, with attributes measured at baseline:
Clients with different personal characteristics/life experiences (e.g., mental illness, trauma history, socioeconomic status, social support).Clients with different manifestations of SUD / patterns of polysubstance use (e.g., opioid use only; opioid use and alcohol; and so on).

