### Randomization procedure

#### Step 1: flagging potentially eligible clients

Clients who meet the inclusion criteria are *potentially* eligible for randomization. We worked with developers responsible for maintaining the community-based public health center’s centralized case management system called CRCT/Cricket (Confidential Record of Consumer Treatment) that is overseen by a community-based public health organization. These developers created a set of decision rules that randomize clients at intake who both meet the above *person-*level eligibility criteria and meet the following *visit-*level eligibility criteria. Since the *same person* might have *multiple visits* to the participating treatment centers, this visit-level eligibility criteria help ensure that those with multiple visits remain in the group tied to their *first intake* within the study window, as opposed to being re-randomized to potentially different groups each time. More specifically, the visit-level rules are:

A new record has been created for the client.The client has not already been enrolled in the study (to prevent clients who return to one of the participating treatment centers multiple times from receiving repeated “doses”).The client meets other sample criteria (age 18 or older).

Once a treatment client has been identified as *eligible for randomization*, they are invited by research staff to then consent to participation in the study. Clients are provided a release of information consent by research staff, affording researchers permission to speak to them as their identity as a recipient of SUD services is protected. Upon signed release of information consent, researchers provide and go over the study consent form with clients. For clients identifying as having literacy challenges, researchers read the consent and all subsequent written material.

Clients *eligible for randomization* then fall into two groups. For prospective participants who *do not* consent to the study and/or sign the release of information, CRCT removes them from the study’s enrollment tables. For prospective participants who *do* consent to the study *and* sign the release of information, they proceed to the randomization step. Participants can discontinue participation at any time by declining consent or revoking consent and notifying the PI they wish to revoke consent. Assignment to the intervention is not blinded.

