### Data sources

#### Survey for baseline attributes

In-depth life course history online surveys will be administered to all consenting clients at both centers who meet sample criteria at intake. Surveys will be completed electronically on secure servers using Qualtrics. Both treatment and control samples complete the life course history survey. Participants are compensated with a one-time $30 Visa gift card incentive. The survey instrument improves reliability and validity by utilizing published peer-reviewed scales known to be reliable measures. Moreover, original measures were developed, evaluated, and improved utilizing participant-based design that included people who use drugs, SUD clinicians, and persons in recovery from SUD as question writers, focus group participants, and survey testers. The survey asks about past drug and alcohol use patterns, mental and physical health, employment, housing, family arrangements, outstanding legal issues and includes the ACE (Adverse Childhood Experiences) scale, Kessler K6 scale, and peer-reviewed questions from instruments utilized in the Boston Reentry Study [14]. The ACE instrument, which is a widely accepted measure of childhood trauma predictive of adult adversity, is used to evaluate additional barriers related to recovery and increased propensity towards substance misuse [44]. The K6 Kessler scale is utilized to detect moderate mental distress. Survey data will be used to form retrospective life history reports. With these rich data we can better isolate correlations between background and recovery and understand who struggles most with substance use and legal issues and what their triggers are. We can also examine baseline equivalence between participants randomized to the treatment and control groups. Consent and survey documents are available upon request to the PI.

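### The survey treated as baseline comes after unblinded allocation and the intervention, so the balance check and subgroups built on its current-state items are not protected by randomisation

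*Protocol article*

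**What the plan says.** The Randomization procedure section numbers its steps. In Step 1, eligible clients are asked for a release of information and study consent. The same step states: "Assignment to the intervention is not blinded". In Step 2 the CRCT system allocates those who consent, after which "Each group then proceeds to their respective intervention". The next two headings are "Step 3: treatment group participants receive the intervention" and "Step 4: both treatment and control group participants complete the life-course history survey". Under the latter: "We invite participants in both groups, using a standard script, to complete our life-course history survey".

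Under Data sources, the same instrument appears beneath the heading "Survey for baseline attributes". It covers past substance use, mental and physical health (with the K6), employment, housing, family arrangements, outstanding legal issues and the ACE scale. One stated use is: "We can also examine baseline equivalence between participants randomized to the treatment and control groups".

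Aims and objectives asks, for the primary question: "do we see heterogeneous effects across the following subgroups of clients, with attributes measured at baseline". The examples given are mental illness, trauma history, socioeconomic status, social support and pattern of substance use.

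**The concern.** A covariate can safely define a subgroup, serve as an adjustment variable or test balance only if allocation could not have affected it. A questionnaire filled in after open allocation, and after one arm has had staff help with its legal problems, does not meet that condition for every item.

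There are two routes to trouble:

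- **The answers may move.** A session that uncovers a warrant, or begins to resolve one, could change reported distress or reported legal issues.
- **The responders may differ.** People whom staff have just helped may accept the survey invitation more often than people who were offered nothing.

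Heterogeneity of effect is one of three named question sets. If a subgroup variable is affected by treatment, the treated and control members of that subgroup are no longer comparable. The balance check loses its meaning as well: an imbalance may be an early effect of the intervention, and an absence of imbalance does not vouch for the allocation.

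**Working it through.** **1. Order of events.** Consent (Step 1), allocation (Step 2), intervention (Step 3), survey (Step 4). No section puts the survey ahead of allocation. The survey section does mention intake, but the phrase may describe when eligibility is met rather than when the survey is taken. Step 1 also places randomisation at intake, so neither reading moves the survey ahead of Step 2.

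**2. Which items are exposed.**

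| Survey content | Can the true value change after allocation? | Can reporting or response differ by arm? |
|---|---|---|
| K6 distress, housing, employment, family and social support, outstanding legal issues | Yes | Yes |
| Demographics, ACE, past use history | No | Yes |

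**3. Which analyses depend on them.** The balance check is tied to the survey explicitly. The subgroup attributes match the survey's topics but are not tied to it. Mental health diagnoses and substance use history are also listed in the section on treatment case files, which states no pre-allocation cut-off date. The primary outcome comes from medical records. The intention-to-treat analysis in Statistical methodology is a difference in means, with linear and logistic regression on the offer. No survey covariate is named.

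**4. How large could it be?** The protocol gives no figure on this point. Its sample sizes for a 10-point improvement reproduce with the usual two-proportion formula (computed 712, 776 and 398; stated 712, 775 and 398), but nothing here depends on them. The following are illustrations on assumed inputs, all with perfect randomisation and no true effect on completion.

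*(a) Balance test.* Assume 400 responders per arm and a scale shifted by d standard deviations in one arm after allocation. The chance that a two-sided 5% test flags imbalance is about Φ(d√(400/2) − 1.96).
- d = 0.1: Φ(1.414 − 1.96) = 29%
- d = 0.2: Φ(2.828 − 1.96) = 81%
- d = 0.3: Φ(4.243 − 1.96) = 99%
- d = 0: the nominal 5%

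*(b) Subgroup membership.* Assume half the clients are truly high-distress, with completion 60% in low and 40% in high distress. Suppose the intervention moves a fraction m of treated high-distress clients into the low category before the survey. Treated completion in the low group is (0.5×0.60 + 0.5m×0.40)/(0.5 + 0.5m), against 60% in controls.
- m = 5%: 0.31/0.525 = 59.0%, difference −1.0 point
- m = 10%: 0.32/0.55 = 58.2%, −1.8 points
- m = 20%: 0.34/0.60 = 56.7%, −3.3 points

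The high group shows no difference here. If instead the clients who move are those with better prognosis (60% completion), the artefact falls in the high group: (0.40 − 0.60m)/(1 − m) − 0.40 = −1.1, −2.2 and −5.0 points. So even the subgroup in which the artefact appears cannot be predicted.

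*(c) Response.* Assume 50% completion in each arm, response rate r, and completion q among non-responders. Completion among responders is [0.50 − (1 − r)q]/r.
- r = 95% v 85%, q = 20%: 51.6% v 55.3%, difference −3.7 points
- r = 95% v 90%, q = 35%: 50.8% v 51.7%, −0.9 points
- r = 95% v 93%, q = 40%: 50.5% v 50.8%, −0.2 points
- equal response: 0

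**The case against.** The strongest reply is that the main result does not use the survey. That stands. A reader might infer that the primary comparison is biased by adjustment for survey items, but no section plans such adjustment or restricts the analysis to responders, and estimation detail is deferred to a later pre-analysis plan.

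Other parts of the reply also stand:

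- Outstanding legal issues, the item most directly exposed, is not among the listed subgroups.
- Childhood adversity and past use cannot truly be changed by a legal-help session, and some attributes could come from the medical record. It would be wrong to say that every subgroup rests on post-treatment data.
- Table 1 puts T0, elsewhere called baseline, in the post-allocation column with the interventions. However, it has no survey row and T0 there marks outcomes, so it is weak evidence on survey timing.
- A standard script and a $30 card limit differential response. The gap between Steps 3 and 4 is unstated and may be short. Courts are said to respond generally within three days, so full resolution before the survey may be uncommon.
- Illustration (c) concerns an overall comparison among responders, which nobody plans. If the bias were equal across subgroups, it would cancel from the contrast between them. Setting it against the 10-point effect that sizes the full sample would mislead.

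What does not stand is the suggestion that a survey close to intake is therefore a baseline survey. A short gap limits how far answers can move, but it does not place the survey before allocation.

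**Conclusion.** The concern holds with limited scope and moderate severity. The stated procedure puts the survey after open allocation and after the intervention, while the data-sources section treats it as baseline. The balance check, and any subgroup analysis or adjustment that uses current-state survey items, is therefore not protected by randomisation. Time-invariant items keep their true values but remain open to responder selection. The unadjusted primary intention-to-treat comparison is unaffected.

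The size of the bias is unknown. It is near zero if answers and response do not differ by arm. It is about 1 to 3 points within a subgroup if 5% to 20% of treated high-distress clients change category, and 5 points in the most extreme scenario shown. Every input to these figures is an assumption, so none should be quoted as the trial's bias. That subgroups will come from the survey is also an inference from matching topics, though the limited CRCT intake fields noted in Step 2 make it likely.

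**What to change.** **New participants.** Give the survey after consent and before CRCT allocation, and add a survey row to Table 1 before allocation. Both arms already consent before allocation and both already take the survey, so this changes the order and adds no new procedure. The cost is real, however. The survey is lengthy and treatment can last as little as one day, so some consenting clients, especially those with very short stays, may leave before being randomised. That could slow enrolment and tilt the randomised sample towards clients who stay long enough to finish.

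**Participants already enrolled** (likely, since registration was retrospective). Record the survey date relative to allocation and first ODR contact, and report survey response by arm. Take subgroup, balance and any adjustment variables only from records dated before allocation, or from time-invariant survey items such as demographics, ACE and past use history. State that responder selection remains a limitation for the survey items. The cost is some data work and the loss of current-state survey items as effect modifiers in this group.

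**Text.** Reconcile the baseline label and the mention of intake in the survey section with Steps 2 to 4, so that one survey time point is stated throughout.

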### Treatment intervention: hands-on-help with ODR platform software

Here we describe the two components of the treatment intervention. First is the platform software itself. Second is the hands-on-help navigating this platform. Based on our focus groups, each component is potentially important for addressing the needs of those with SUD.

#### Component one: ODR platform software

The tech start-up Court Innovations has [7] software tools offered in fifty-one districts throughout Michigan. The software resolves what are considered “minor” legal disputes, but among the substance using community these minor legal disputes can present major obstacles to participating fully in recovery, as well as with obtaining housing, a job, or reuniting with family. Software tools include Warrants, Amnesty, Friend of the Court (child support enforcement), Driving While License Suspended, Online Plea, and Ability-to Pay. The online platform allows clients to communicate with judges, clerks, and prosecutors remotely (at the court’s discretion), complete forms, upload, and sign documents for the court, and resolve outstanding legal obligations electronically, including vacating warrants without ever stepping foot in the courthouse. Court officials offer the client a resolution or request more information. The process is streamlined in a user-friendly online forum that can be accessed from any mobile device. Documents may be uploaded via smartphone photos.

The software has the following features that might be especially useful for those in treatment for SUDs:

**Reducing stigma felt during face-to-face court appearances**: reducing the need to come into court to describe one’s substance misuse in public can be extremely valuable and destigmatizing. Personal dialogue has been demonstrated to be easier to share over an online platform than in front of community members in open court [34, 35].**Access during all hours rather than just court hours**: The platform is accessible 24 hours a day, seven days per week and courts generally respond within three days or less [34].^4^ The 24-hour a day access can be important for clients whose residential treatment makes workday court appearances challenging.**Mobile friendly**: The software is intended as a user-friendly online forum that can be accessed from any mobile device. Documents may be uploaded via smartphone photo. Research staff can facilitate mobile upload on research team devices or help facilitate permission and access for clients to utilize their own mobile device for this purpose. This eliminates the need for clients to track down computer equipment like a scanner, which may be unavailable to them during clinical treatment. The supportive nature of the intervention and mobile capabilities help overcome barriers for many clients who otherwise have no or limited access to mobile devices while in treatment.

While these features of the ODR software are promising and some recent scholarship has found evidence that ODR and virtual court proceedings, which carry similar features to ODR—namely not having to go into the courthouse—can improve access to justice for vulnerable clients [34, 42], other scholarship found that technologies can *widen* rather than *reduce* inequalities if they are not straightforward to use for marginalized populations [43]. Therefore, we view the software alone as a necessary but not sufficient intervention for resolving legal issues among those with SUDs. We now turn to the second component, which is meant to help make the ODR software accessible to participants.

#### Component two: hands-on-help with the ODR platform software

The second component for treatment group participants is hands-on help with the ODR software. Participants in this group will be introduced to ODR and given staff assistance in utilizing the tool for online legal resolution. Participants lacking technological literacy will be offered direct support from research staff who will walk them through the web content and read all electronic content to the participant.

### Control group

Participants randomized to the control group could technically access the ODR software, which is free and available to members of the public. Yet to do so, they would [1] need to seek out the platform on their own and [2] navigate the technological barriers to using the software for unresolved legal issues. Our fieldwork in treatment centers shows that we expect low control group uptake of the software due to inpatient clients’ lack of access to technology, low or limited levels of technology literacy for many clients in our participant demographic, combined with low literacy levels reported among many clients, and lack of knowledge that this resource exists or how to navigate it successfully. While inpatient, clients have very limited access to phones and computers, and internet access is generally limited to scheduled and monitored supportive services with a staff member present, such as completing an application for food assistance. Approximately 1 in 3 clients identifies as having literacy difficulties, either with reading, with technology, or a visual impairment that inhibits their ability to access and utilize a web browser without a support person. Finally, like many public resources, uptake rates can be limited among vulnerable populations, who may not know the resource exists and have barriers to accessing it successfully.

### Sample size justification

We intend to enroll 800 participants, with half of the clients randomly assigned to treatment (hands-on training with free ODR) and the other half randomly assigned to the control group (no ODR). A list of final study site locations may be requested from the primary investigator (PI). To determine whether we are sufficiently powered to detect an effect, we conducted a power analysis focused on the primary outcome: the client’s compliance with the treatment plan. We calculate the sample size needed for the study by applying the significance level of 0.05 and 80% power for a two-sided test. Since we lack both site-specific base rates of compliance and data on the possible effect size of hands-on training with ODR, we analyzed power along different dimensions of [1] base rates of treatment plan compliance in the control group and [2] possible improvements in compliance from the hands-on training with ODR. We set cases when the control group’s base rate of the treatment plan compliance ranges from 0.3 to 0.8 and then estimate the sample size necessary when the treatment group turns out to show 2–15% improvement from the control group. From this calculation, we find that 712 participants are necessary to find the difference between the compliance rate of 30% and 40% between the control and the treatment group. When the base rate of treatment plan compliance is 50% for the control group and 60% for the treatment group, we need 775 participants to find the distinction. If the compliance rate for the control group is 80%, 398 participants can inform us of the 10% difference between the two groups. Based on the result, we conclude that 800 participants allow us to detect a ~ 10% point improvement or larger; if compliance rates are high, we can detect much smaller improvements.

### Study outcomes

The study outcomes in both groups will be measured at baseline (T0) and at one year (T1) and two years (T2) after baseline. The primary outcome will be substance use behaviors, which we use electronic medical records data to measure. Secondary outcomes measured with administrative data include (i) mortality, (ii) employment and earnings, (iii) justice system involvement, e.g., civil and criminal legal system encounters, (iv) housing status and household composition.^5^Table 1 shows the SPIRIT flow diagram for the schedule of enrollment, intervention and assessment.

**Table 1 Tab1:** SPIRIT diagram for the schedule of enrolment, interventions, and assessments

	Study period				
	Enrolment	Allocation	Post-allocation	Post-allocation year 1	Post-allocation year 2
Timepoint	- t1	0	T0	T1	T2
Eligibility	X				
Informed consent	X				
Allocation		X			
Interventions:					
Intervention group			X		
Control group			X		
Assessments:					
Primary Outcome			X	X	X
Secondary Outcome			X	X	X

The primary outcomes of interest are substance use behaviors. The secondary outcomes of interest are (i) mortality, (ii) employment and earnings, (iii) justice system involvement, e.g., civil and criminal legal system encounters, (iv) housing status and household composition (see Footnote 5)

The study outcomes will be measured at baseline (T0) and at year 1 (T1) and year 2 (T2) for both groups

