### Participants and clinical setting

The study inclusion criteria are (i) adult (aged 18 years or older), (ii) client receiving direct addiction recovery services at either partnering not-for-profit treatment center, (iii) Medicaid recipient or uninsured.

Participants may be male, female, or non-binary. Participants may be on probation or parole, but do not have to be. People who cannot read or lack computer literacy are eligible and will be offered direct support on these measures from research staff. Participants are offered the research instruments in English and may request a native Spanish speaking research team member and Spanish language research instruments during enrollment.

Two treatment centers are participating in our intervention and have multiple clinical and residential locations throughout Southeast Michigan, including over 180 transitional housing beds scattered throughout the county. Site locations include detoxification, inpatient, outpatient, and transitional housing. All clients are selected from a centralized case management system managed by a local public health agency that serves uninsured and Medicaid clients only. Length of treatment varies from 1 day up to about 2 years. Clients may be referred by friends, family, or law enforcement but also engage services on their own accord. One treatment center partner describes that their referrals often come from “courts, Friend of the Court [child support enforcement], Child Protective Services, Secretary of State, private attorneys, and other service agencies” [19]. Some clients are mandated to treatment in lieu of incarceration and may face incarceration if they fail to comply with the terms of treatment. Clients who participate in standard Drug Court or Sobriety Court typically are ordered to two years of intense supervision by a team of specialists which includes treatment components, but the specified treatment regimen, e.g., detoxification, residential, transitional housing, etc. varies by client.

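### The outcome that is powered (treatment-plan compliance) is not the outcome named as primary (substance use behaviors), and no primary time point is fixed

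*Protocol article*

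**What the plan says.** The protocol article describes the primary endpoint in several places.

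- **Study outcomes**: "The primary outcome will be substance use behaviors, which we use electronic medical records data to measure". The Table 1 note repeats this in the plural. The secondary outcomes listed there are mortality, employment and earnings, justice-system involvement, and housing and household composition.
- **Sample size justification**: "we conducted a power analysis focused on the primary outcome: the client’s compliance with the treatment plan". The calculation is described as "applying the significance level of 0.05 and 80% power for a two-sided test", and the target follows: "We intend to enroll 800 participants".
- **Aims and objectives, primary aim**: "the client’s compliance with goals he or she has set for their own treatment and recovery".
- **Aims and objectives, primary question**: "does offering clients access to and hands-on-guidance with ODR to resolve legal issues increase the client’s likelihood of completing treatment".
- **Data sources**: the section on treatment case files, whose heading is about treatment plan compliance, says that primary outcomes come from electronic medical records. Its list of fields includes compliance with treatment and substance use history.
- **Abstract, Methods**: the primary objective is long-term recovery together with fewer adverse health, economic, justice-system and housing outcomes.

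On timing, Study outcomes gives baseline, one year and two years for both groups, and Table 1 marks the primary outcome at T0, T1 and T2. On the length of treatment, Participants and clinical setting says: "Length of treatment varies from 1 day up to about 2 years".

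**The concern.** Two consecutive sections each say what the primary outcome is, and they name different things. These are not two labels for one variable. A client can finish a programme and later use substances, or keep to a plan without finishing. Nor does substance use behaviors read naturally as an umbrella term for the others: Table 1 schedules the primary outcome at baseline, where completion of a newly opened episode has no informative value.

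Two things are at stake. The first is that the 80% power statement belongs to one outcome while the outcomes section and the SPIRIT table give primary status to another. The second is that a reader cannot tell which result, at which time, would confirm or refute the hypothesis. That matters more than usual here because assignment is not blinded and the trial was registered retrospectively, so the published protocol is one of the few places where the confirmatory test could have been pinned down.

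**Working it through.** **Step 1. Reproduce the stated sample sizes.** Inputs from Sample size justification: two-sided 0.05 (z = 1.960), 80% power (z = 0.8416), control and treatment rates of 30/40%, 50/60% and 80/90%. Allocation is 1:1 (Randomization procedure, Step 2). The pooled two-proportion formula without continuity correction is

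n per arm = [1.960·√(2·p̄·(1−p̄)) + 0.8416·√(p₁(1−p₁) + p₂(1−p₂))]² / (p₂−p₁)²

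- 30 v 40%: [1.960·√0.455 + 0.8416·√0.45]² / 0.01 = 355.9 per arm, total 711.9. Stated: 712.
- 50 v 60%: [1.960·√0.495 + 0.8416·√0.49]² / 0.01 = 387.3 per arm, total 774.7. Stated: 775 (776 if each arm is rounded up).
- 80 v 90%: [1.960·√0.255 + 0.8416·√0.25]² / 0.01 = 199.0 per arm, total 397.9. Stated: 398.

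The arithmetic is sound, and it is arithmetic for a binary rate.

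**Step 2. Power at the planned size for that binary rate.** With 400 per arm, z = [0.1·√400 − 1.960·√(2·p̄·(1−p̄))] / √(p₁(1−p₁) + p₂(1−p₂)):

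- 30 v 40%: z = 1.011, power 84.4%.
- 50 v 60%: z = 0.887, power 81.3%.
- 80 v 90%: z = 2.021, power 97.8%.

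The smallest difference detectable with 80% power at 400 per arm is 9.4 points from a base of 30%, 9.8 from 50% and 7.3 from 80%. This agrees with the article's claim of about 10 points.

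**Step 3. The same calculation for substance use behaviors.** It cannot be done. The article gives no measure (binary, count, scale or time to event), no control-group rate or standard deviation, and no effect size. The case-file section lists substance use history but defines no follow-up measure of use.

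**Step 4. Set the sections side by side.**

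| Place | Outcome treated as primary | Powered? |
|---|---|---|
| Sample size justification | Treatment-plan compliance | Yes |
| Data sources, case files | Plan compliance, by its heading | Same outcome |
| Primary aim | Compliance with client's own goals | Plausibly the same outcome |
| Primary question | Treatment completion | Only if defined as the same binary rate |
| Study outcomes, Table 1 note | Substance use behaviors | No |
| Abstract, primary objective | Long-term recovery and four outcome domains | No |

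Reading goal compliance and plan compliance as one construct leaves three distinct candidates in the body of the article: compliance, completion and substance use.

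**Step 5. Time point.** Two follow-up times are scheduled and neither is designated primary. With treatment lasting from one day to about two years, completion or compliance may be settled well before T1 for some clients and still open at T1 for others. The choice between T1 and T2 therefore changes what is being measured.

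**The case against.** The strongest defence is that this is a condensed article that promises a later pre-analysis plan, and that most of it points one way: the power section, the case-file heading and the primary aim all concern compliance. Part of this stands. Goal compliance and plan compliance may well be a single outcome, so counting four incompatible primaries would overstate the conflict. The sample size is also sound for the outcome it was computed for.

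The defence does not reach the core. Statistical methodology defers the estimation approach to the later plan; it does not defer which outcome is primary. The conflict is stated in the text, and a later plan that chose one outcome would still contradict part of this article.

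Some stronger readings are tempting but unsupported.

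- *Unequal follow-up between arms.* A reader might infer this from "at years one and two following the intervention", since the control group has no intervention. That phrase belongs to the secondary questions. Study outcomes counts from baseline in both groups, and Table 1 labels its columns by time since allocation.
- *Goals rewritten after unblinded allocation.* Nothing in the article says that client goals are or can be revised after randomisation.
- *An inflated type I error of a given size.* No section plans separate tests at 0.05 across outcomes or times, so any family-wise figure would describe an analysis that the article does not propose.

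**Conclusion.** The point holds. The article names conflicting primary outcomes, and its 80% power at two-sided 0.05 attaches to a binary compliance-type rate, not to the substance use behaviors named in Study outcomes and the Table 1 note. The compliance outcome that is powered is absent from that section altogether. No primary time point is named.

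For plan compliance, 800 participants give 81% to 98% power across the three 10-point scenarios shown. For substance use behaviors the power is unknown and cannot be bounded from the document. A reader might infer that 800 is too few, or that no outcome in the trial is powered. Neither follows: the defect is that the sections do not match, not that the number is wrong.

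The conclusion assumes that plan compliance would be analysed as a binary rate, as the power section does, and that the footnotes, whose text is not in the copy reviewed, do not redefine the primary outcome. It needs correction before analysis because the confirmatory test is not identified.

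**What to change.** Name one primary outcome, with one measure and one time point counted from randomisation in both arms. Then align the abstract's primary objective, Aims and objectives, Sample size justification, Study outcomes, Table 1 with its note, and the case-file section with it.

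- **Choice that keeps the stated sample size:** the binary treatment-plan compliance outcome already powered. State how it relates to completing treatment in the primary question. Make substance use behaviors and the other follow-up time secondary.
- **If the sponsor keeps substance use behaviors as primary:** define the measure, and redo the 80% power statement for it or withdraw it.
- **If completion is chosen:** define it from a field that the records hold, say how clients still in treatment at the chosen time are counted, and confirm that the 30–80% range of base rates used for compliance is reasonable for it.

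The first option costs only wording. The second needs a new calculation, and possibly a different sample size. Under any option at least one outcome now described as primary loses that status. The choice is the sponsor's, and it should be made and dated before outcome data are examined by arm.
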